#### **4.9.5 Subgroup analyses**

The Cox and Poisson models described in sections 4.9.2 and 4.9.3 will be conducted according to the following baseline subgroups:

- Baseline glycaemic status: prediabetes vs normoglycaemia
- Gravida: 1 vs >1
- Country: Bangladesh, India, Sri Lanka
- Body mass index (BMI): underweight (<18), normal (18-25), overweight (>25-30), obese (>30)
- Insulin use in index pregnancy: yes vs no
- Time since GDM-affected pregnancy: above vs below or equal to median
- Age: above vs below or equal to median

This will be done by adding the corresponding subgroup variable to the main Cox and Poisson models as a fixed effect together with its interaction with the randomised group. Heterogeneity by subgroup will be quantified by the p-value associated with the interaction term. Results will be presented on forest plots.

#### **4.9.6 Sensitivity analyses using HbA1c and FBG results**

Analyses described in Sections 4.9.1, 4.9.2 and 4.9.3 will be repeated while using FBG and HbA1c values where an OGTT was not performed as scheduled during a follow-up visit. Censoring will occur

at the time of the last relevant measure of glycaemia. For visits where an OGTT was performed, glycaemic categories will be defined according to the definition of Section 4.9. Otherwise, the following hierarchical approach will be used:

- 1) For those with both HbA1c and FBG data available:
  - a. T2DM: **HbA1c  $\geq 6.5\%$  or FBG  $\geq 126$  mg/dL**
  - b. Normal glucose tolerance: **HbA1c  $< 5.7\%$  and FBG  $< 100$  mg/dL**
  - c. Pre-diabetes: everyone else
- 2) For those with only HbA1c data available:
  - a. T2DM: **HbA1c  $\geq 6.5\%$**
  - b. Normal glucose tolerance: **HbA1c  $< 5.7\%$**
  - c. Pre-diabetes: everyone else
- 3) For those with only FBG data available:
  - a. T2DM: **FBG  $\geq 126$  mg/dL**
  - b. Normal glucose tolerance: **FBG  $< 100$  mg/dL**
  - c. Pre-diabetes: everyone else

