**Scenario 2: OGTT at <24 weeks of gestation (scenario of second preference)**

[figure not shown]

**Scenario 3: FPG at <24 weeks of gestation (least favoured scenario)**[figure not shown]

These individuals will receive standard GDM care, but will also be exposed to an additional brief standardised educational program to improve knowledge of nutrition and physical activity both during and after pregnancy. The study will also be discussed, as establishing rapport with the participants at this stage will be important to maximise participation in post-pregnancy screening. Further contact will be made with potential participants on at least one occasion after hospital discharge, and prior to 3 months post-childbirth, when women will be invited for an OGTT to determine trial eligibility. Those diagnosed with T2DM using ADA criteria at this time will be referred for appropriate care; all other women will be eligible for trial participation.

The *inclusion* criterion, therefore, is the absence of T2DM (i.e. confirmation of NGT, IFG, or IGT) at 3 to 18 months post-partum OGTT. Consistent with design features of a pragmatic trial [29], *exclusion* criteria will be limited to:

- Confirmed case of Type 2 Diabetes

- Travel time to hospital more than 2 hours (unless individual circumstances will not impede hospital attendance for study visits)
- Lack of access to a mobile telephone
- Use of steroids during pregnancy other than for lung maturation of the baby
- Likelihood of moving residence in the next 3 years

All reasons for exclusion or consent refusal will be carefully recorded.

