#### 5.1.2 Registration visit (3-18 months post-partum)

1. Perform OGTT and measure HbA1c.
2. If OGTT indicates T2DM, refer for care; if OGTT does not indicate T2DM, invite patient to participate in trial, and arrange randomisation visit appointment (could be same day).

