## 2.6 Sample Size

A sample size of 1414 women with GDM will provide 90% power ( $2\alpha=0.05$ ) to detect a relative risk of 0.65, assuming that the control group cumulative incidence for change in glycaemic category will be 20% at 24 months and allowing for 20% of missing outcome data.

The initial power calculation was based on a chi-square test comparing two proportions at 24 months; however, to account for various study durations, the primary analysis will consist in a survival analysis of time to change in glycaemic category which is expected to have at least the same power as a comparison of proportions.

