### 4.1 General Principles

Analyses will be performed using SAS Enterprise Guide version 8.3 or higher (SAS Institute Inc., Cary, NC, USA).

All variables will be analysed by descriptive statistical methods. The number of data available and missing data, mean, standard deviation, minimum, quartiles, median, and maximum will be calculated for continuous data. Frequency tables will be generated for categorical data. For categorical variables, the number and percentage of patients with a specific level of the variable will be presented.

All tests will be two-sided with a type-I error rate of 5%. Analyses of the primary outcome (change in category of glycaemia from normoglycaemia to IGT, IFG or T2DM or from IFG or IGT to T2DM) will be unadjusted for multiplicity; however, we will control the family-wise error rate across secondary outcomes using a Holm-Bonferroni correction [2]. No other multiplicity adjustment will be applied.

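### The HbA1c branches of the SAP 4.9.6 sensitivity analysis compare an OGTT-defined baseline with an HbA1c-defined follow-up, so some women with unchanged HbA1c are counted as events

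*Combined protocol and SAP*

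**What the plan says.** **Baseline.** Protocol 3.2 makes trial entry depend on "absence of T2DM (i.e. confirmation of NGT, IFG, or IGT) at 3 to 18 months post-partum OGTT". At registration (Protocol 5.1.2) the site is to "Perform OGTT and measure HbA1c", and the OGTT alone decides whether the woman is invited. Registration HbA1c is therefore planned for every woman, but it sets neither eligibility nor the baseline category.

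**Event.** SAP 2.4.1 and 4.9 count a move from normal glucose tolerance (NGT) to IFG, IGT or T2DM, or from IFG or IGT to T2DM. All categories are defined by OGTT glucose limits.

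**Sensitivity analysis.** SAP 4.9.6 repeats 4.9.1 to 4.9.3 "using FBG and HbA1c values where an OGTT was not performed as scheduled during a follow-up visit". Where an OGTT was done, its category stands. Otherwise:

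- HbA1c with FBG: T2DM if HbA1c is at least 6.5% or FBG at least 126 mg/dL; normal if HbA1c is below 5.7% and FBG below 100; pre-diabetes in all other cases.
- HbA1c only: the same HbA1c limits.
- FBG only: the same FBG limits.

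Nothing in 4.9.6 uses registration HbA1c, requires a rise from it, or deals with women already above a limit.

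**The concern.** An event should mean that the woman's glycaemia got worse. Under 4.9.6 it can also mean that the test changed. HbA1c and the OGTT are different measures, and the plan gives no reason to expect every woman classed NGT by OGTT to have HbA1c below 5.7%. Any who do not are turned into events by the switch of test.

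This matters because 4.9.6 is the plan's main check on missed OGTTs. SAP 3.10 imputes nothing unless stated, and the Poisson analysis in 4.9.3 keeps the same event and censoring definitions as the Cox model. Table 8 gives the HbA1c/FBG version its own rows for the primary outcome and for T2DM, and Figure 4 repeats the survival plots for it. If its ratio lies closer to 1 than the primary result, a reader cannot tell whether the effect is fragile or the test changed.

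**Working it through.** **1. Apply the rules to women whose values do not change.** FBG and 2-h glucose are in mg/dL.

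| Values at baseline and follow-up | Baseline (OGTT) | HbA1c only | HbA1c + FBG | FBG only |
|---|---|---|---|---|
| FBG 90, 2-h 120, HbA1c 5.5% | NGT | normal, no event | normal, no event | normal, no event |
| FBG 90, 2-h 120, HbA1c 5.8% | NGT | pre-diabetes, **event** | pre-diabetes, **event** | normal, no event |
| FBG 90, 2-h 160, HbA1c 5.8% | IGT | pre-diabetes, no event | pre-diabetes, no event | normal, no event |
| FBG 90, 2-h 160, HbA1c 6.6% | IGT | T2DM, **event** | T2DM, **event** | normal, no event |

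The FBG-only branch cannot produce a false event from unchanged values. OGTT-defined NGT already requires FBG below 100, and any woman without T2DM has FBG below 126. These are the limits that 4.9.6 uses. A check over FBG 60 to 125 and 2-h glucose 60 to 199 found none.

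**2. Reproduce the design figure.** SAP 2.6 plans "to detect a relative risk of 0.65", with "control group cumulative incidence for change in glycaemic category will be 20% at 24 months" and "allowing for 20% of missing outcome data". That is 0.20 against 0.65 × 0.20 = 0.13. With 90% power and two-sided 5%, the pooled two-proportion formula is

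n = [1.960 √(2 × 0.165 × 0.835) + 1.282 √(0.20 × 0.80 + 0.13 × 0.87)]² / 0.07² = 589 per arm, or 1178 in total.

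1178 × 1.2 = 1413.6, which rounds to the planned 1414. (Dividing by 0.8 would give 1473. That is a separate matter and does not bear on this point.) The design rates of 20% and 13% are therefore a sound starting point.

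**3. Add false events equally to both arms.** Let a be the share of women who become false events, independent of true progression. The observed risk is a + (1 − a)p, so

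RR observed = (0.13 + 0.87a) / (0.20 + 0.80a).

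| a (assumed) | Control | Intervention | RR observed |
|---|---|---|---|
| 0 | 0.2000 | 0.1300 | 0.65 |
| 2% | 0.2160 | 0.1474 | 0.68 |
| 5% | 0.2400 | 0.1735 | 0.72 |
| 8% | 0.2640 | 0.1996 | 0.76 |

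**4. What could give such shares.** For the NGT route, a = (share NGT at baseline) × q × v. Here q is the share of NGT women with registration HbA1c at or above 5.7%, and v is the share of those classified at least once by HbA1c without an OGTT. The pilot in Protocol 2.1 had 28% NGT and 40% IFG/IGT, so 28/68 = 41% of women without T2DM were NGT. The documents give neither q nor v.

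| q (assumed) | v (assumed) | a | RR observed |
|---|---|---|---|
| 10% | 25% | 1.0% | 0.667 |
| 20% | 50% | 4.1% | 0.712 |
| 20% | 100% | 8.2% | 0.758 |

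The effect runs from negligible to material, depending on two quantities that the plan does not report.

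**The case against.** The strongest reply is that few women are exposed. Much of it stands.

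- **Which visits are filled.** If 4.9.6 covers only scheduled OGTTs that were missed, the visits are Months 12, 24, 36 and end of study. Protocol Table 3 plans no HbA1c at the 12-monthly visits, so a missed annual OGTT would usually leave FBG or nothing, and HbA1c would come in mainly at end of study. If the word that opens the hierarchy in 4.9.6 also takes in the planned HbA1c visits at Months 6, 18 and 30, v approaches 1 and false events start at Month 6. The text allows both readings.
- **Lockdown.** A reader might infer that lockdown visits drive the problem. The remote visits described under Protocol Table 3 collected neither OGTT nor HbA1c, and both tests were to follow once restrictions lifted. Only visits with HbA1c but no OGTT are exposed.
- **The T2DM route.** At Months 6, 18 and 30 a high HbA1c calls for an OGTT, which then takes priority in 4.9.6. The route stays open only where that OGTT is not done, or at end of study if the OGTT is missed. (The Table 3 footnote sets the trigger at 6.5% or above, while Protocol 5.1.4 sets it above 6.5%. The two must be reconciled.) No OGTT is triggered between 5.7% and 6.5%, so the NGT route is not closed.
- **Power.** A reader might turn the attenuation into a loss of power. At a = 5%, power is 78.9% with 565.6 women per arm (1414 × 0.8 / 2), but 87.1% with 707 per arm if the women with missing OGTTs are the ones being filled in. The plan states no power for this analysis, so neither figure should be claimed.
- **Visibility.** Table 4 already reports OGTT, HbA1c and FBG availability by visit and arm. That would show a difference between arms in OGTT completion, but not how many events came from the change of test.

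**Conclusion.** The point holds for the two branches of SAP 4.9.6 that use HbA1c. It follows from rules the plan states, not from detail left out. An NGT woman with registration HbA1c from 5.7% to below 6.5% becomes an event without any change. An IFG or IGT woman at or above 6.5% can become T2DM if no OGTT intervenes.

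The 0.68, 0.72 and 0.76 rest on three assumptions: false-event shares of 2%, 5% and 8%, equal shares in both arms, and a comparison of cumulative proportions as a stand-in for the hazard ratio. The shares are illustrative.

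A reader might infer that the main trial result is at risk. It is not: the primary analysis is the OGTT-only Cox model (SAP 4.9.2 and the Table 8 footnote). A reader might also infer that the bias is always towards 1. That follows only if the false events are equally common in both arms. The trial is open-label and OGTT completion could differ by arm, so the direction is not guaranteed.

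**What to change.** Add to SAP 4.9.6:

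> At a visit classified using HbA1c (with or without FBG), an event requires a category worse than both the participant's baseline OGTT category and her baseline category derived from the same measure(s) at registration. Where registration HbA1c is missing or already at or above 6.5%, that visit is classified by FBG only.

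Both comparisons are needed. With the same-measure comparison alone, a woman with IGT whose HbA1c moves from 5.5% to 5.8% would become an event although she stays pre-diabetic, which is not an event under SAP 2.4.1.

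Also state whether the planned HbA1c visits at Months 6, 18 and 30 are included, and report the number of events by source (OGTT, HbA1c with FBG, HbA1c only, FBG only) in each arm.

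The cost is a short SAP addition and one table; registration HbA1c and fasting glucose are already collected. The downside is that slightly fewer events count in this sensitivity analysis: a woman who starts with NGT and HbA1c of at least 5.7% can no longer have a pre-diabetes event at an HbA1c-classified visit, and a visit with neither a usable HbA1c nor FBG stays unclassified.

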## 4.9 Analysis of the primary outcome

The primary outcome is a change of glycaemic category, at or prior to final visit defined as:

- A change from Normal glucose tolerance (NGT) to impaired fasting glucose (IFG) or impaired glucose tolerance (IGT), or T2DM
- A change from IFG or IGT to T2DM

This will be diagnosed using ADA criteria as given below:

- Normal glucose tolerance (<100 mg/dL fasting and <140 mg/dL post-glucose load)
- Impaired glucose tolerance (<100 mg/dL fasting and 140-199 mg/dL post-load)
- Impaired fasting glucose (100-125 mg/dL fasting and <140mg/dL post-load)
- Type 2 diabetes ( $\geq 126$  mg/dL fasting or  $\geq 200$  mg/dL post-load)

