### 4.9.1 Descriptive analyses

The number and proportion of subjects in each glycaemic category will be reported by group and by visit according to the six following categories:

- 1) Normoglycaemia
- 2) IFG
- 3) IGT
- 4) IFG + IGT
- 5) T2DM
- 6) Unknown glycaemic status

This will be done both using a table and a stacked bar chart.

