**Table 4. Participant disposition by visit**

|                                | Intervention
N=() | Control
N=()    | Total
N=()      |
|--------------------------------|----------------------|--------------------|--------------------|
| Randomisation           |                      |                    |                    |
| Assessed                | xxx (xx.x%)   | xxx (xx.x%) | xxx (xx.x%) |
| With OGTT data                 | xxx (xx.x%)          | xxx (xx.x%)        | xxx (xx.x%)        |
| No OGTT but HbA1c and FBG data | xxx (xx.x%)          | xxx (xx.x%)        | xxx (xx.x%)        |
| With HbA1c data only           | xxx (xx.x%)          | xxx (xx.x%)        | xxx (xx.x%)        |
| With FBG data only             | xxx (xx.x%)          | xxx (xx.x%)        | xxx (xx.x%)        |
| Not assessed            | xxx (xx.x%)   | xxx (xx.x%) | xxx (xx.x%) |
| Completed expected FU          | xxx (xx.x%)          | xxx (xx.x%)        | xxx (xx.x%)        |
| Discontinued due to pregnancy  | xxx (xx.x%)          | xxx (xx.x%)        | xxx (xx.x%)        |
| Discontinued due to T2DM       | xxx (xx.x%)          | xxx (xx.x%)        | xxx (xx.x%)        |
| LTFU / unknown reason          | xxx (xx.x%)          | xxx (xx.x%)        | xxx (xx.x%)        |
| Month 6                 |                      |                    |                    |
| Assessed                | xxx (xx.x%)   | xxx (xx.x%) | xxx (xx.x%) |
| With OGTT data                 | xxx (xx.x%)          | xxx (xx.x%)        | xxx (xx.x%)        |
| No OGTT but HbA1c and FBG data | xxx (xx.x%)          | xxx (xx.x%)        | xxx (xx.x%)        |
| With HbA1c data only           | xxx (xx.x%)          | xxx (xx.x%)        | xxx (xx.x%)        |
| With FBG data only             | xxx (xx.x%)          | xxx (xx.x%)        | xxx (xx.x%)        |
| Not assessed            | xxx (xx.x%)   | xxx (xx.x%) | xxx (xx.x%) |
| Completed expected FU          | xxx (xx.x%)          | xxx (xx.x%)        | xxx (xx.x%)        |
| Discontinued due to pregnancy  | xxx (xx.x%)          | xxx (xx.x%)        | xxx (xx.x%)        |
| Discontinued due to T2DM       | xxx (xx.x%)          | xxx (xx.x%)        | xxx (xx.x%)        |
| LTFU / unknown reason          | xxx (xx.x%)          | xxx (xx.x%)        | xxx (xx.x%)        |

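### In the SAP 4.9.6 sensitivity analysis, a fasting glucose below 100 mg/dL on its own is scored as normal glucose tolerance, so isolated IGT cannot be detected at a fasting-only visit, yet that visit still extends event-free follow-up

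*Combined protocol and SAP*

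**What the plan says.** SAP 4.9 classifies each OGTT by two values. The normal category is "Normal glucose tolerance (<100 mg/dL fasting and <140 mg/dL post-glucose load"; the IGT category is "Impaired glucose tolerance (<100 mg/dL fasting and 140-199 mg/dL post-load". Diabetes is fasting at or above 126 mg/dL or post-load at or above 200 mg/dL. A move from normal to IGT is a primary-outcome event (SAP 2.4.1 and 4.9).

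SAP 4.9.2, the primary analysis, censors event-free women at their last OGTT. SAP 4.9.6 repeats 4.9.1 to 4.9.3 using HbA1c and fasting glucose where a scheduled OGTT was not done. The third tier, "For those with only FBG data available", has three rules: 126 mg/dL or above is diabetes; below 100 mg/dL is normal, written "Normal glucose tolerance: FBG $< 100$ mg/dL" (rule 3b here); all others are pre-diabetes. Censoring is then "at the time of the last relevant measure of glycaemia".

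SAP 4.9.1 already has a category "Unknown glycaemic status", and SAP Table 4 has a row "With FBG data only" at each visit. The SAP does not say that a fasting value below 100 mg/dL alone leaves glucose tolerance undetermined.

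**The concern.** Rule 3b gives a definite label that the SAP's own definitions do not allow from a fasting value alone. The visit cannot show one kind of primary-outcome event, yet it counts as evidence that no event occurred and moves the censoring date forward. Baseline status comes from an OGTT, so the yardstick also changes between baseline and follow-up. In the repeated 4.9.1 table, a woman with unchanged isolated IGT appears to have returned to normal.

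This matters because 4.9.6 is the only planned analysis I can find that brings in women whose OGTT was missed. The Poisson analysis (4.9.3) uses the same event and censoring definitions as the Cox model, and SAP 3.10 rules out imputation unless explicitly stated. After the March 2020 lockdown changes, readers will look to 4.9.6 for reassurance. The trial is open-label, so test completion could differ by arm.

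**Working it through.** **Step 1. Set 4.9 beside rules 3a to 3c.** I classified every pair of whole-number values (fasting 60-159, 2-hour 60-299 mg/dL) both ways. The counts are grid cells, not frequencies of women.

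| Fasting | 2-hour | SAP 4.9 | Fasting-only tier | Pairs |
|---|---|---|---|---|
| <100 | <140 | Normal | Normal | 3200 |
| <100 | 140-199 | IGT | Normal | 2400 of 2400 |
| <100 | ≥200 | Diabetes | Normal | 4000 of 4000 |

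All isolated IGT is labelled normal, as is all diabetes shown only by the 2-hour value with fasting below 100. No data are needed for this result. The first error costs an event only in women normal at baseline; the second can affect any woman, and also the T2DM outcome in Table 8.

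**Step 2. Size.** The plan states no figure on this point and gives neither the number of fasting-only visits nor the share of events visible from fasting. Inputs:
- Risk 0.20 in both arms (no true effect); 20% is the control incidence in SAP 2.6.
- s, the share of women whose last visit is fasting-only: assumed 0.10 in control and 0.20 in intervention.
- v, the share of events visible from fasting: assumed 0.3 to 0.7.

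Observed risk = 0.20 × [1 − s(1 − v)]; HR = ln(1 − risk, intervention) / ln(1 − risk, control).

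| v | Control risk | Intervention risk | HR |
|---|---|---|---|
| 0.3 | 0.186 | 0.172 | 0.917 |
| 0.5 | 0.190 | 0.180 | 0.942 |
| 0.7 | 0.194 | 0.188 | 0.966 |

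Reversing the shares gives the reciprocals: 1.09, 1.06 and 1.04.

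**Step 3. Allow for earlier OGTTs.** Step 2 assumes that every event in a woman with a fasting-only last visit could be found only at that visit. Protocol 5.1.4 schedules OGTTs at Months 12, 24 and 36. If half of these women's events were caught earlier (an assumption), s(1 − v) halves and the HRs become 0.96, 0.97 and 0.98. For these shares, step 2 is therefore an upper bound on the bias.

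**Step 4. Equal shares.** With the same s and v in both arms, both null risks shrink by the same factor and the HR is 1. The cost is events. At the design values (1414 × 0.8 / 2 = 565.6 per arm, 20% against 13%), the expected number is 565.6 × 0.33 = 187, and the chi-square power is 0.888, close to the stated 90%. Losing 5%, 10% or 15% of events equally leaves 177, 168 or 159 and power of 0.869, 0.847 or 0.823; the risk ratio stays at 0.65.

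**Step 5. A tempting repair that fails.** Suppose only the fasting values that prove an event were kept, and all other fasting-only visits dropped. With v = 0.4, the control risk is 0.20 × (1 − 0.10 × 0.6) / [1 − 0.10 × (1 − 0.20 × 0.4)] = 0.188 / 0.908 = 0.207. The intervention risk is 0.176 / 0.816 = 0.216. HR = ln(0.784) / ln(0.793) = 1.05, so the bias changes direction.

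**The case against.** The strongest reply is about scope. The confirmatory result uses OGTTs only, and Table 8 shows it beside the 4.9.6 result. An analysis that substitutes cruder tests must misclassify some women, and a later OGTT can still record a missed event, though late. All of this stands, so a reader should not infer that the primary hazard ratio is biased or that every such conversion is lost for good.

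Second, the row in Table 4 might be read as proof that fasting-only visits are expected. It is not: the same row stands in the randomisation block, although eligibility requires an OGTT, so it looks like a repeated template. Protocol 5.1 schedules no standalone fasting test. Such visits are nevertheless possible: at Months 12, 24 and 36 an OGTT is scheduled without HbA1c, so a test that yields only its fasting sample falls into tier 3.

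Third, deleting tier 3 would discard sound information. Fasting at or above 126 mg/dL meets the diabetes definition by itself, and fasting of 100-125 mg/dL in a baseline-normal woman already proves worsening. This is a good reason to keep the tier and test its influence.

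Fourth, the tiers with HbA1c (1b and 2b) also assign normal without a 2-hour value. That is correct and should be acknowledged with 3b; it does not make 3b consistent with 4.9.

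**Conclusion.** The contradiction holds on the SAP's own cut-offs and is confined to the 4.9.6 sensitivity analysis and its tables, including the T2DM rows. At a fasting-only visit, isolated IGT, and diabetes shown only by the 2-hour value with fasting below 100, are scored as normal, and event-free time is added.

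The practical size is unknown, because fasting-only visits are not counted. Equal shares by arm make events and absolute rates too low without biasing a null hazard ratio. Bias in the ratio needs a difference between arms. At an assumed 10% against 20%, the null hazard ratio goes no lower than 0.92 to 0.97 (v of 0.3 to 0.7), and lies nearer 1 if earlier OGTTs catch some events. A reader might infer that the plan favours the intervention; the documents give no figure for a difference between arms, and the opposite imbalance would bias the other way. The point deserves correction, but it does not threaten the primary analysis.

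**What to change.** 1. Keep the tiered analysis in 4.9.6, and repeat it with fasting-only visits coded "Unknown glycaemic status" and censoring at the last OGTT or HbA1c. In the repeat, do not retain only the fasting values that prove an event (step 5 of the working). Side by side, the two versions show how much rests on tier 3.
2. Add a fasting-only analysis in which baseline and every follow-up visit, OGTT visits included, are classified by fasting glucose alone (<100, 100-125, ≥126 mg/dL). Label it fasting-defined worsening.
3. Footnote Table 8 and the repeated Table 7: rule 3b cannot detect isolated IGT, and rules 1b and 2b also assign normal without a 2-hour value.

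All of this uses data already held. The cost is SAP wording and extra table rows. The repeat analysis uses fewer visits and sets aside some fasting values that already meet the event definition. The fasting-only endpoint does not include IGT, so it is a different question from the primary outcome and must be labelled so.
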